**Fig. 1 Fig1:**
[figure not shown]
The study flow chart

**Table 1 Tab1:**
[figure not shown]
The experimental process and evaluation

### Interventions

Gasless vNOTES has been emergingly used recently, whereas the literature comparing the advantages between traditional vNOTES and gasless vNOTES is limited. Thus, we want to compare gasless vNOTES vs. traditional vNOTES on hemodynamic profiles and outcomes in patients with benign gynecological disease.

#### Intervention description

##### Anesthesia management and study intervention

The participants are continuously monitoring when they enter the operating room, including electrocardiograph (ECG), pulse oximetry, and non-invasive blood pressure. For the induction of the anesthesia, the patients are administered sulfentanyl (0.3 µg/kg), propofol (2 mg/kg), and cisatracurium (0.15 mg/kg) intravenously. Then, sevoflurane is adjusted for maintaining anesthesia and achieving a target BIS between 40–60 during the surgery. A single injection of sulfentanyl (0.1 µg/kg) and a bolus dose of cisatracurium (0.05 mg/kg) are permitted to be given independently during the surgery if necessary. When the surgery is completed, the patients are reversed with neostigmine 0.04 mg/kg and atropine 0.02 mg/kg if their TOF ratio is less than 0.9. Tracheal extubation is performed after the patient is fully awake and follows instructions.

If the patient’s MAP decreases > 20% compared to the baseline, the patient is given an intravenous injection of phenylephrine 40 µg. If the patient’s HR is detected to be less than 50 bpm, atropine will be given 0.3 mg per time. In the case when MAP increases to more than 30%, nitroglycerin 100 µg per time is administered.

##### Surgical technique

Since surgical proficiency may be one of the major potential influenced factors affecting the outcomes, all surgeries are performed by the specialist surgeons with more than 3 years of experience in performing vNOTES. All patients are placed in the lithotomy position. Standard vaginal and abdominal preparation is performed in all of our patients in case of conversion to transabdominal surgery. A Foley catheter is inserted to drain the urinary during surgery. The vaginal incision is made around the cervix.

For patients who allocate to the traditional vNOTES group, after insertion of one port through the vagina, CO_2_ gas is infused with a pressure of 12–14 mmHg. A 10-mm rigid 0°laparoscope is used, and energy devices to coagulate and remove the diseased tissue according to the location of the lesion. After the procedure is completed, vaginal cuff closure is done extracorporeally with continuous locking suture with 1–0 vicryl.

For patients who are allocated to the gasless vNOTES group, a special device is used as an abdominal wall-lifting device. One point is placed at the adnexa surface projection on the abdominal wall to establish the operating space, and the other point is placed under laparoscopic observation to facilitate gasless surgery. CO_2_ pneumoperitoneum will not be used during the whole procedure (Fig. 1).

After the surgery, patients will be transferred to the post-anesthesia care unit (PACU).

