#### Allocation, Randomization, and blinding

This is a randomized, double-blind controlled clinical trial. One hundred and twenty patients will be recruited and randomly assigned to either the traditional vNOTES group or the gasless vNOTES group in a 1:1 ratio. A researcher from the anesthesiology department who is not involved in the current study will generate the randomized allocation number and distribute the allocated opaque envelope. The envelope will be delivered directly to the surgeon who is responsible for performing the surgery. The researchers involved in the postoperative assessment and the researchers analyzing the data are blinded to the groups’ assignment. When consent for trial participation is obtained from the participant, the physician will double-check the medical number, age, gender, and primary disease of the participant before unsealing the envelope to avoid reallocation and confirm their allocation. The study flow chart is presented in Fig. 1. The study process and evaluation are reported in Table 1. This study is in accordance with SPIRIT reporting guidelines, which are attached as an online Supplemental file 1.

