### Data collection

The following data will be collected during the study. To guarantee the study quality, all the investigators will be trained and pass the examinations. The trained investigator (YW) who will be blinded to the allocation will collect intraoperative data. KL, QH, and QZ will do the anesthesia procedures and collect intraoperative data, respectively; to avoid bias, they will not participate in postoperative data collection. All the statistical analyses will be performed by one of the corresponding authors (YC).Demographic data: Age, BMI, ASA status, clinical diagnosis, history of spontaneous delivery, abdominal surgery history, and surgical index.Intraoperative data: The MAP and HR prior to induction (T0), at the time point of intubation (T1), 10 min after tracheal intubation (T2), surgical incision immediately (T3), 10 min after surgical incision (T4), 10 min before the end of surgery (T5), at the end of surgery (T6), and at the time point of tracheal extubation (T7); duration of surgery; duration of anesthesia; the consumption of anesthetics (including sufentanil and cisatricurium); consumption of vasoactive drugs (including nitroglycerin and metaraminol); intraoperative estimated blood loss. Intraoperative complications include bowel, ureter, and bladder injury.Postoperative data*Postoperative pain assessment* All patients will be guided to use a 0 to 10 cm visual analogue Scale (VAS) to express the degree of pain. VAS scores are collected at the time of 2 h after surgery and 24 h after surgery. Additional analgesic medications are available at the patient’s request. Number of patients who have a requirement for rescue analgesia are recorded. Postoperative rescue analgesia can be provided by intravenous injection of 5 μg sufentanil or ketorolac 30 mg.*Postoperative adverse events *The incidence of postoperative nausea and vomiting (PONV) during postoperative 24 h are recorded. Nausea is referred to the patient with uncomfortable feeling in their stomach, and the severity of nausea is evaluated as follows*:* none = 0, mild = 1, moderate = 2*.* If there is gastric content vomited out, it is scored as 3. Rescue antiemetic could be offered to any patient who has a nausea score > 2. Postoperative complications include surgical site infection within 14 days, and unplanned secondary surgery related to this surgery.

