### Statistical methods

Data will be analyzed by using R studio 4.2.2 for Windows (Armonk, NY, United States). Data from the primary outcome will be presented as mean ± standard deviation if normally distributed, and t-test will be conducted; otherwise, the data will be reported as median (IQR), and no-parametric tests will be performed. Categorical data will be summarized as frequencies (percentages) and compared between study groups using χ2 tests or Fisher exact tests, as appropriate. *P* value < 0.05 was considered significant.

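### Surgical proficiency is named as a major influence, but surgeon enters neither the stated allocation nor the stated tests; adjusting for it is a cheap gain in precision, not the repair of a bias

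*Protocol article*

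**What the plan says.** **Surgeons.** The Surgical technique section says: "Since surgical proficiency may be one of the major potential influenced factors affecting the outcomes, all surgeries are performed by the specialist surgeons". The entry rule that follows is more than 3 years of experience in vNOTES. Surgeons are in the plural and their number is not given. The rule concerns vNOTES in general, not the gasless technique under test.

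**Allocation.** The section on allocation, randomization and blinding gives 1:1 individual allocation of 120 patients and mentions no stratification. It adds: "The envelope will be delivered directly to the surgeon who is responsible for performing the surgery". The surgeon is therefore attached to the case before the arm is known.

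**Anaesthesia.** The Data collection section says that three investigators "will do the anesthesia procedures and collect intraoperative data, respectively". The last word leaves open which of them gives anaesthesia and which records data.

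**Data and tests.** The listed baseline items are: "Age, BMI, ASA status, clinical diagnosis, history of spontaneous delivery, abdominal surgery history, and surgical index". Neither surgeon nor anaesthetist appears there or among the intraoperative items. The Statistical methods section says: "Data from the primary outcome will be presented as mean ± standard deviation if normally distributed, and t-test will be conducted". Otherwise a nonparametric test is used, and categorical data get a χ2 or Fisher test. No covariate is mentioned. No other test is named for continuous secondary outcomes such as duration and blood loss, so I take the same tests to apply to them.

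**The concern.** The plan identifies a factor that it believes may drive outcomes, then carries it into neither the stated allocation nor the stated analysis. An experience threshold sets a floor; it does not make surgeons equal. Surgeons who all meet it may still differ in operating time and blood loss, both secondary outcomes. Any such difference widens the standard error of the treatment comparison when surgeon is left out.

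Anaesthesia matters for the primary outcome. Sevoflurane is titrated within a BIS range, and supplementary boluses are given at discretion. Both can move MAP and HR. The surgeon is evidently fixed before the envelope is opened, which makes surgeon a legitimate pre-randomisation covariate. The article says nothing equivalent about the anaesthetist.

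At stake are some precision on the secondary outcomes, and a reader's ability to see how operators were spread across the arms.

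**Working it through.** The article gives no figure for operator effects, so there is none to reproduce. Its sample size concerns a binary blood-pressure outcome and is not an input here.

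**Inputs from the article.** 60 patients per arm, individual 1:1 allocation, no stated stratification; one-sided α of 0.05 and 80% power, used only as a reference level.

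**Assumptions.** Between-operator share of outcome variance ρ from 0 to 0.20; 2 to 4 equally busy operators. The documents give neither.

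**1. Is the unadjusted test valid?** I take the outcome as operator effect (variance ρ) plus residual (variance 1 − ρ), with operator independent of arm and no treatment effect. In 20,000 simulated trials per scenario, a two-sided 5% t-test rejected in 4.78% to 5.16% of trials across ρ = 0, 0.05, 0.10 and 0.20 with 2, 3 and 4 operators. It keeps its level.

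**2. How uneven can the operators be by chance?** For one operator with share q of the cases, the SD of the difference in that share between arms is √(2q(1 − q)/60).

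| Operators | q | SD | 95% range (±1.96 SD) |
|---|---|---|---|
| 2 | 1/2 | 0.091 | ±18 points |
| 3 | 1/3 | 0.086 | ±17 points |
| 4 | 1/4 | 0.079 | ±16 points |

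With three operators of 40 cases each, the chance that at least one is split 25:15 or worse is about 39% under simple randomisation, and about 19% if the arms are forced to 60/60. Visible imbalance is thus quite likely, but step 1 shows that the unadjusted test already allows for it.

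**3. What does adjustment gain?** Removing between-operator variance multiplies the standard error by √(1 − ρ). With 80% unadjusted power, power becomes Φ[(1.645 + 0.842)/√(1 − ρ) − 1.645]. For ρ = 0.10 this is Φ(2.487/0.949 − 1.645) = Φ(0.976) = 83.5%.

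| ρ | SE ratio | Power after adjustment | Per-arm n equivalent to 60 unadjusted, 60(1 − ρ) |
|---|---|---|---|
| 0 | 1.000 | 80.0% | 60.0 |
| 0.02 | 0.990 | 80.7% | 58.8 |
| 0.05 | 0.975 | 81.8% | 57.0 |
| 0.10 | 0.949 | 83.5% | 54.0 |
| 0.20 | 0.894 | 87.2% | 48.0 |

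**4. What does adjustment cost?** Step 3 ignores the degrees of freedom spent. For three operators (two extra parameters), an approximate ratio is √((1 − ρ) × 117/115).

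- ρ = 0: 1.009, power about 79.4%
- ρ = 0.05: 0.983, power about 81.2%
- ρ = 0.10: 0.957, power about 83.0%
- ρ = 0.20: 0.902, power about 86.7%

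Adjustment breaks even at ρ = 1 − 115/117, about 1.7%. Below that it costs at most about 0.6 of a power point.

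**The case against.** The strongest objection is that this is an omission from a condensed article. The article refers to a CRF that is not shown, and a full protocol or SAP may hold operator fields and a covariate list. Nothing says that operator goes unrecorded or that adjustment is ruled out. This stands as far as recording is concerned, so I do not conclude that the data are missing. It does not fully dispose of the analysis, because the article goes beyond silence: it names the tests, and it names proficiency as a major influence.

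The objection also points to safeguards: the experience rule, training and examination of investigators, weight-based induction doses, a BIS target and numeric triggers for vasoactive drugs. These narrow operator differences and make a low ρ plausible. That stands too, and is why the range starts at zero.

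Four stronger readings are tempting, and the documents do not support them:

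- *That an operator imbalance could not be corrected later.* Operation and anaesthetic records would normally identify the operators. What would be lost is pre-specification.
- *That the unadjusted comparison is biased or confounded.* Allocation is individual and random, and the surgeon is already responsible for the case when the envelope arrives. Chance imbalance is sampling variation.
- *That the anaesthetist is chosen after the arm is known.* The article is silent on when the anaesthetist is assigned, and silence is not evidence.
- *That several people certainly give anaesthesia.* The wording on the division of duties allows that reading but does not establish it.

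**Conclusion.** The point holds as a modest, inexpensive improvement. The plan's unadjusted comparisons are valid, but they leave between-surgeon variation in the error term although the plan itself regards proficiency as important. From 80% power, the gain is nil at ρ = 0, under 2 points at 5%, about 3.5 at 10% and about 7 at 20%, before a cost of roughly half a point for the degrees of freedom with three operators. These sizes rest on an assumed ρ and an assumed number of operators, and on approximately normal outcomes. For the primary outcome the case is weaker than for duration and blood loss, because it is unclear whether more than one person gives anaesthesia and much of the anaesthetic is standardised.

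**What to change.** 1. Record operating surgeon and anaesthetist for every patient, if the CRF does not already do so. For patients already enrolled, take both from the operation and anaesthetic records.
2. Before the data are analysed, pre-specify surgeon as a factor alongside arm in the comparison of surgery duration and blood loss. If these are skewed, use a rank test stratified by surgeon.
3. Name the anaesthetist before the envelope is unsealed. State who gives anaesthesia and who records data. If more than one person gives anaesthesia, report MAP and HR adjusted for anaesthetist as a sensitivity analysis.
4. Tabulate surgeon and anaesthetist by arm.
5. Do not put surgeon in a model for conversion if events are few. With 60 per arm and no conversion rate given, such a model could be unstable.

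The cost is two fields from routine records, one or two sentences in the analysis section, and one degree of freedom fewer than the number of operators in each model. No extra patients are needed. If operators do not differ, the gain is negligible.

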##### Criteria for discontinuing or modifying allocated interventions

Patients can quit the study at any time during the procedure, regardless of any reason. The investigators can discontinue patients’ participation if they are allergic to sedatives, have serious adverse events, are reluctant, or cannot be assessed after the procedure.

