## Abstract

**Background:**

Literature regarding the advantages of gasless vNOTES is insufficient. The aim of our study is to compare gasless vNOTES vs. traditional vNOTES on hemodynamic profiles and outcomes in patients with benign gynecological disease. We hypothesize that compared with those in the traditional vNOTES group, hemodynamic profiles will be changed less during gasless vNOTES, while safety can be promised.

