### Data management and confidentiality

The CRF is designed according to our protocol and deposited in our special safe. Only the study team member who has permission from the principal investigator has access to this safe. Data will be entered into an electronic database and double-checked by the third investigator (DF). Any missing data or errors in the data will be summarized along with detailed descriptions and will be queried by checking the original forms. When the study is completed, the key to safety will be preserved by the principal investigator (YC) who is one of the corresponding authors. The detailed identification of the enrolled patients will not be reported in publications.

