### Outcome measures

1. The primary outcome is vital signs at the different time points, including before anesthesia (baseline: T0), at endotracheal intubation (T1), 10 min after endotracheal intubation (T2), at the beginning of the operation (T3), 10 min after the operation (T4), 10 min before the end of the operation (T5), at the end of the operation (T6) and at the time of tracheal extubation (T7).2. The second outcomes are collected as follows.①Surgical conversion rate refers to the surgeon cannot complete the surgery in the scheduled mode of operation, and has to convert to open abdominal surgery or traditional multiport laparoscopic surgery, or single port laparoscopic surgery. For the patient who is allocated to the gasless vNOTES group, the surgeon requires the use of traditional vNOTES with CO_2_ pneumoperitoneum if they are unable to complete the surgery under gasless vNOTES, and this patient is considered as a surgical conversion. If the operation cannot be completed according to the scheduled surgical method, the surgical strategy can be changed as appropriate.② Duration of surgery (from speculum placement to suturing the wound)③ Duration of anesthesia (from anesthesia induction to endotracheal extubation)④ The anesthetic consumption during the surgery, including sufentanil and cisatracurium⑤ Intraoperative estimated blood loss⑥ VAS and PONV scores at postoperative 2 h and 24 h.⑦ Administration of vasopressor drugs from the beginning of general anesthesia induction to 15 min after endotracheal intubation, including times, dosage, and type.⑧ Intraoperative and postoperative complications (e.g., bowel, ureter, and bladder injury, surgical site infection, and unplanned secondary surgery).⑨ Time of first getting out of bed after surgery⑩ Time of first eating after surgery after surgery, including light drink.

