### Safety, adverse event reporting, and harms

Each safety issue will be defined when one or more of the following respective criteria are met. Intraoperative complications include bowel, ureter, and bladder injuries related to surgical technique. Postoperative complications referred to surgical site infection within 14 days, and unplanned secondary surgery associated with this surgery.

Adverse events are defined as all undesirable symptoms that may have a potential association with the investigational procedures. All adverse events are shared with the investigators and will be dealt with timely and appropriate. Serious adverse events related to this trial will be reported to the Chengdu Women’s and Children’s Central Hospital Certified Review Board (CRB) within 10 days.

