### Sample size estimation

The sample size calculation was based on the changes in patients' blood pressure at the beginning of surgery. Since no similar studies have been conducted before, a pilot study was conducted previously. According to the results of the pilot study, in the traditional vNOTES group, 50% of patients had a greater than 20% change in blood pressure at the beginning of the CO_2_ pneumoperitoneum. Due to the different surgical strategies, CO_2_ pneumoperitoneum is not required in the gasless vNOTES group. We assume that the number of patients with a blood pressure change of more than 20% is less in the gasless vNOTES group than in the traditional vNOTES group. The 10% reduction in the gasless vNOTES group was considered to be statistically significant. A statistical power of 80% and a one-sided α significance level of 0.05 were used for power analysis with 1:1 allocation. A sample size of 49 patients in each arm was estimated. Considering a dropout rate of 20%, 60 patients for each group were enrolled.

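### Investigators may end a patient's participation because of a serious adverse event or because she cannot be assessed, which permits outcome-dependent loss from safety follow-up

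*Protocol article*

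**What the plan says.** The rule stands in the protocol article under Criteria for discontinuing or modifying allocated interventions. The heading concerns the intervention, but what the sentence allows investigators to discontinue is the patient's "participation if they are allergic to sedatives, have serious adverse events, are reluctant, or cannot be assessed after the procedure". The rule is discretionary. A separate sentence lets patients leave whenever they wish.

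Other sections that bear on it:

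- **Hypothesis** (Abstract and Background): "hemodynamic profiles will be changed less during gasless vNOTES, while safety can be promised". Safety is part of what the trial sets out to show.
- **Outcome measures**, eighth secondary outcome: "Intraoperative and postoperative complications (e.g., bowel, ureter, and bladder injury, surgical site infection, and unplanned secondary surgery". The sixth covers pain and nausea scores at 2 h and 24 h.
- **Safety, adverse event reporting, and harms**: "Postoperative complications referred to surgical site infection within 14 days, and unplanned secondary surgery associated with this surgery". The same section states "All adverse events are shared with the investigators and will be dealt with timely and appropriate", and then "Serious adverse events related to this trial will be reported to the" hospital's review board, within 10 days.
- **Data management and confidentiality**: "Any missing data or errors in the data will be summarized along with detailed descriptions", with queries checked against the original forms.
- **Sample size estimation**: 49 per arm, and then "Considering a dropout rate of 20%, 60 patients for each group were enrolled".

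**The concern.** A rule for stopping a treatment and a rule for leaving a study do different things. The first may be needed for the patient's care. The second stops data from being collected. Here a heading about the first introduces a sentence about the second.

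Two triggers matter most. A serious adverse event and not being assessable both occur after randomisation, and either can be a consequence of the operation received. If participation ends for such a reason, the patients lost are not a random subset. A patient with an organ injury, for example, is one in whom a later infection or re-operation most needs to be recorded.

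The comparison at stake is of complications between the arms. Few events can be expected with 60 patients per arm, so the loss of one or two could change how that comparison reads. An analysis plan written later can define who is analysed, but it cannot recover follow-up that the protocol allowed to stop.

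**Working it through.** **1. What is collected before and after a discontinuation could take effect**

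| Data (Data collection; Outcome measures) | When | Exposed to the rule? |
|---|---|---|
| Blood pressure and heart rate, T0 to T7 | up to extubation | not by a later discontinuation |
| Bowel, ureter and bladder injury | recorded as intraoperative data | the event itself is captured |
| Conversion | during surgery | not a trigger, and counted as an outcome |
| Pain and nausea scores | 2 h and 24 h | yes |
| First time out of bed, first intake | after surgery | yes |
| Surgical site infection | to day 14 | yes |
| Unplanned secondary surgery | after surgery, no time limit given | yes |

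The exposure is therefore in postoperative follow-up, and possibly in whether the patient is counted in the comparison at all.

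**2. Can the sentence be read as concerning the intervention only?**

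For the trigger about assessment after the procedure, it cannot. By then the operation is over and no allocated intervention is left to stop. Acting on that trigger can only take the patient out of follow-up or out of the study.

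**3. Does the article elsewhere keep such patients in?**

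Reporting to the review board makes a trial-related serious event known to the board. It does not keep the patient in follow-up or in the between-arm comparison. Describing and querying missing data records a gap without preventing it. Nowhere does the article say that a discontinued patient continues to day 14.

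**4. The plan's own figure for patients leaving**

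Inputs: 49 evaluable per arm and 20% dropout (Sample size estimation).

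- 49 × 1.20 = 58.8, so 59.
- 49 / (1 − 0.20) = 61.25, so 62.
- Stated: 60, within two patients of either.

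The margin over the target is 60 − 49 = 11 per arm. It is a recruitment margin and says nothing about why patients leave.

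**5. Illustration of sensitivity (assumed counts)**

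The article gives no complication rate, so the counts below are assumptions. Suppose x of 60 patients in one arm have a complication and all x leave the comparison. The upper limit is the exact two-sided 95% limit: the 0.975 quantile of Beta(x + 1, n − x), which for x = 0 is 1 − 0.025^(1/n).

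| Assumed x | All counted | Upper limit | x patients gone | Upper limit |
|---|---|---|---|---|
| 1 | 1/60 = 1.7% | 8.9% | 0/59 | 1 − 0.025^(1/59) = 6.1% |
| 2 | 2/60 = 3.3% | 11.5% | 0/58 | 1 − 0.025^(1/58) = 6.2% |
| 3 | 3/60 = 5.0% | 13.9% | 0/57 | 1 − 0.025^(1/57) = 6.3% |

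The right-hand columns show the extreme case, in which every affected patient leaves together with her data. The document does not say that this happens. The table shows only how few removals it would take to change the picture.

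**The case against.** The strongest reply is that the rule says participation can be ended and says nothing about discarding data. Intraoperative injuries are collected as intraoperative data, adverse events are shared with the investigators, trial-related serious events are reported, and missing data are summarised and queried. The analysis set may be defined in a full protocol or analysis plan that is not shown, and its absence from an article is no fault. All of this stands. A reader might infer that the events behind the safety claim are removed, but the text does not support that. What remains is a rule that is stated, and that lets follow-up end for reasons linked to outcome.

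Other stronger readings also go beyond the document:

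- **Conversion rates biased downwards.** Conversion is not a trigger, and Outcome measures counts a converted patient as a conversion.
- **The haemodynamic comparison broken.** The T0 to T7 readings end at extubation, and nothing says that a later discontinuation discards them.
- **The dropout allowance licenses exclusions.** It is a recruitment margin, not permission to exclude.
- **Decisions made by people who know the arm.** The surgeon knows it, but the article does not say which investigators decide, and it blinds the postoperative assessors.
- **Safety to be concluded from non-significant P values.** Statistical methods names tests for categorical data and attaches no safety decision to them.

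Finally, the article does not define a serious adverse event. Its examples of severe events, under Data monitoring, are cardiac arrest and severe bleeding, while organ injuries are listed separately as complications. The overlap between trigger and outcome is therefore plausible but not stated.

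**Conclusion.** The point holds in a limited form. As written, the rule permits loss from postoperative follow-up, and possibly from the between-arm safety comparison, for reasons that arise after randomisation and may depend on the technique. It does not delete recorded events, and it does not touch the conversion outcome or the primary readings.

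The size cannot be taken from the document. Under assumed counts of one to three affected patients in an arm of 60, a complication rate of 1.7% to 5.0% would become zero if those patients left the comparison with their data. This rests on two assumptions: that some serious events are also complication outcomes, and that patients whose participation ends are neither followed nor counted. The article neither confirms nor rules out the second.

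The direction of any bias depends on which arm loses more such patients. If the losses follow harm, the arm with more harm would look better than it is.

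**What to change.** Reword the section so that stopping the allocated intervention and leaving the study are two separate things. For example:

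*Stopping or changing the allocated intervention does not end a patient's participation. A serious adverse event, or difficulty in assessing the patient after the procedure, does not end data collection. These patients are followed to day 14 for all planned outcomes and are counted in their assigned arm, unless they withdraw consent. Assessments that cannot be made are recorded as missing, with the reason.*

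This concerns data collection only. When the intervention itself should be stopped or changed remains a clinical matter for the investigators.

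The cost is a few sentences and an amendment. The article already provides for protocol changes to go to the review board and the registry. Follow-up to day 14 is already planned, so no visit or procedure is added. Trial status described recruitment as still under way, so the rule could apply to patients yet to enter. For any patient already discontinued on these grounds, the sponsor could check what follow-up was obtained. The downside is that the safety result may turn out slightly less favourable.
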